### Sample size

Based upon previous studies, we expected an absolute difference in cessation rates between the intervention and control group of 5% (with 10% quitting in the intervention group and 5% in the control group) [15,20].

To achieve 80% power with a significance level of 0.05 (2-sided) and correction for continuity, a sample size of 474 persons is needed in each group. If there is 30% attrition in the follow-up measurement the number needed in each group is 677, with the total required sample size being 1,354. The allowance for attrition is deliberately conservative.

### Intervention design and development

Existing guidance for the development of smoking cessation interventions suggests that intervention development should be informed by theory and the existing evidence base [28]. The theoretical models used in previous smoking cessation interventions have mostly been based on social cognitive theory, with tailoring messages by using the transtheoretical model, along with other means of motivational enhancement and psychological support. Supporting self-regulatory skills during the action stage has been shown to be important for a sustainable change of behaviour in young people [9]. However, it remains unclear which particular theories result in the most effective interventions [13], and there is no clear evidence which components or techniques in previous smoking cessation interventions are the most essential to include [29-31].

In the absence of a clear theory to build the intervention, we decided to develop the messages based on existing practice in the form of components of official manuals about smoking cessation recommended in Sweden, as well as using material from books from experienced cessation experts, and key elements from previous SMS-based interventions and Internet- based interventions [12,15,18,20,22-26,32,33]. In order to optimise the participants’ experience of the intervention as a ‘real person’ we were guided by theories of therapeutic relationships [4] and research emphasising the importance of the quality of the actual encounter between client/recipient and professional/caregiver [34,35], as well as on models of the relationships between social interactions, empowerment and health [36]. Efforts were devoted to developing messages that inspired and encouraged participants to increase their ability to mobilise and develop their own resources.

The elements derived from these studies, reviews and interventions used in the present intervention are as follows: making a public declaration about quitting (that is telling friends about the quit attempt); encouraging asking friends and relatives for support; problem solving tips; distraction techniques and the possibility to text for more help if having a slip and starting to crave. All messages were discussed by a multidisciplinary team of researchers with wide experience of life style interventions, in particular SMS- and Internet-based cessation interventions regarding smoking and alcohol.

The basic structure and delivery of the present smoking cessation intervention, called NEXit, was inspired by previous smoking cessation interventions delivered via mobile phone text messaging [17,18,21-25,27]. The central component of these SMS-based interventions was one or more daily text messages tailored to the various phases of quitting smoking: preparation before quitting, the initial quitting phase and the maintenance phase. The length of NEXit was set to 12 weeks in accordance with most previous interventions and recommendations in guidelines [17,18,21-25,27]. In addition to the 12-week core intervention we added a 1- to 4-week motivational phase before setting a stop date, as used in most previous interventions [22-25].

The final NEXit content includes a 1- to 4-week motivational phase and a 12-week core intervention. In the motivational phase the participants receive 2 SMS per day. The messages in the motivational phase contain information relevant in advance of quitting, that is symptoms to expect on quitting, tips to avoid weight gain, tips to cope with cravings and to avoid smoking triggers, motivational support, and how to distract one’s mind from smoking.

The 12-week core programme consists of 157 messages. The participants receive 5 SMS per day 3 days before the quit date. Messages provide information about the consequences of smoking, how to quit and stay having quit. They prompt participants to prepare by getting rid of cigarettes, ashtrays and lighters and to avoid environments where they could normally smoke.

After the quit date the participants will receive 5 SMS per day for the first 3 days and then 4 SMS the rest of the first week. During weeks 2 to 4 the participants receive 2 SMS per day. In weeks 5 to 7 the number of SMS is decreased to 2 SMS every second day and 1 SMS the other days. In weeks 8 to 12 the number of SMS is 1 daily.

Messages encourage participants to persevere with the quit attempt and to focus on their success so far. They are given coping messages for handling cravings, motivational messages, and assistance with withdrawal symptoms. The content covers information relevant to quitting; tips to avoid weight gain and improve nutrition; tips to cope with craving; advice on avoiding smoking triggers; instructions on breathing exercises to perform instead of smoking; motivational support (for example feedback on amount of money and life years saved) and distraction (for example sports, travel, cinema, drinking water).

The intervention includes a function where participants can ask for extra SMS when having problems with craving, relapse or weight gain. By texting the word ‘crave’ participants with cigarette cravings receive three instant messages some minutes apart to distract or support them during these episodes. By texting the word ‘lapse’, participants receive three text messages that encourage them to continue with their quit attempt. By texting ‘weight’, participants receive tips on how to avoid weight gain.

### Earlier work on the feasibility of the intervention

Several steps were taken during the development of the NEXit programme and will be further described here. A first version of the NEXit intervention was developed during the spring of 2013. An expert panel consisting of 10 smoking cessation experts in Sweden evaluated this first version of the intervention during the autumn of 2013 by reviewing all text messages and, based on their feedback, the messages were revised in several iterative steps. Further, a focus group interview with current smokers or smokers who had recently quit was undertaken. The participants were presented with the structure and examples of the content of the programme as part of the interview. The focus group interview was conducted using a semi-structured interview guide in order to collect experiences and points of view regarding structure of the programme, the length, number and content of the messages. The focus group provided generally positive feedback on the structure and content of the intervention.

In the next phase, in late autumn of 2013, 10 smokers were asked to give their opinion about the structure and content of the intervention by reviewing all text messages and giving written feedback to the research team. The purpose of involving smokers individually and in the focus group previously was, in particular, to test and confirm the acceptability of the messages’ number, tone, content and programme duration. Some changes were made to a minority of the messages that were not found appropriate by the smokers. Subsequently, another 8 smokers agreed to test all steps in the intervention from the initial sign-up procedure to the 1- 4-week motivational phase, setting a quit date and receiving the first 4 weeks of the core intervention. Minor revisions were again made.

Based on the above mentioned development steps a second shortened (8 weeks) version of the NEXit intervention was tested in a pilot trial in the winter/spring of 2014 (n = 35) where, besides the content of the messages, the technological feasibility of intervention delivery and study procedures were tested. In the pilot trial all parts of the intervention and data collection were tested and found to work as intended except from some minor but important technical issues that were resolved immediately after the pilot study. After the end of the 8-week intervention, 8 phone interviews were conducted to elicit reactions and opinions on improvements in intervention elements. An interview guide using open-ended questions was used regarding the process of getting started, preparation leading up to quit day, and setting a stop date, as well as on the number of messages, the tone, the timing and the content. The results confirmed that a majority of the participants experienced that the intervention was easy to access, the message content and tone was motivating and helpful, and the intervention included a sufficient number of messages.

Participation in the pilot trial was somewhat lower than expected, and the drop-out at various steps during recruitment and after randomisation was higher than anticipated. Therefore, a number of revisions were made to boost recruitment and prevent attrition before setting a quit date. It was decided that recruitment should not only to be by invitation by mail, but also through posters, leaflets and information on the colleges’ and universities’ homepages during a 1-month period.

### Outcome evaluation

The baseline questionnaire contains 19 questions about sociodemographic data and smoking habits. The participants will be asked to state their age, gender, marital status and years of smoking and, if using Swedish snuff (‘*snus*’), how much per day. Then follows the 6 questions of Fagerström’s Nicotine Dependence Scale and a question on how important it is for the participants to quit smoking with response option on a scale from 1 to 10, where 1 stands for not important at all and 10 very important. All participants will be asked if they ever have tried to stop smoking before (and if so how many times); if they ever have tried nicotine replacement (if so how many times); if they have been prescribed drugs for smoking cessation, and if they have received professional counselling or if they have called the national quit smoking help-line.

After 4 months, a link to an electronic follow-up questionnaire will be Emailed to all participants. Initially, 2 reminders 1 week apart will be sent to non-responders. In order to minimise attrition those participants still not responding will receive additional Email reminders every second day for 6 days (that is 3 Emails). If still not responding, the non-responders will receive a SMS every second day for 6 days (that is 3 SMS) with only 2 questions to answer, to capture the 2 primary outcome measures. Lastly, those still not responding will be phoned with a maximum of 10 calls per participant. Also, in the invitation to answer the follow-up questionnaire the participants will be told that they are offered the opportunity to be part of a draw for a number of iPads (Apple Inc., Cupertino, CA, USA) after having answered the follow-up questionnaire.

Outcome measures are as follows:

*Primary outcome measures*:Self-reported prolonged abstinence (defined as having not smoked more than 5 cigarettes in the last 8 weeks).Self-reported 4-week point prevalence of smoking abstinence (not having smoked a single cigarette).

*Secondary outcome measures*:Self-reported 7-day point prevalence of smoking abstinence (defined as not smoking any cigarettes in the past 7 days).Mean number of quit attempts since taking part in the study.Number of uses of other smoking cessation services (prescribed medication, nicotine replacement medication, counselling, calling the help-line or any other help) since first invitation to the study.Numbers of cigarettes smoked weekly (for participants still smoking at the time of follow-up only.

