### Data analysis

The data analysis will conform to the pre-specified statistical analysis plan described below. The analysis will start after collection of the follow-up data. There will be no interim analyses or stopping rules. Following the intention-to-treat analysis strategy, all analyses will include all participants with follow-up data in their groups as randomised, and sensitivity analyses will include all randomised participants to explore different assumptions about the missing data [37].

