#### Primary analyses

The primary analyses will assume that missing outcome data are missing at random and, therefore, will be performed on complete cases only.

The binary outcomes of self-reported prolonged abstinence, 4-week prevalence of smoking abstinence and 7-day point prevalence of smoking abstinence will be analysed by logistic regression and results presented as odds ratio (95% CI). Number of quit attempts and number of uses of other smoking cessation services will be analysed by negative binomial regression and results presented as ratio of means (95% CI). Numbers of cigarettes smoked weekly will be analysed by logarithmic transformation and linear regression and results presented as ratio of geometric means (95% CI).

All regression analyses will be adjusted for by the following baseline variables: gender, years of smoking, average number of cigarettes smoked weekly, severity of dependence as measured by Fagerström’s Nicotine Dependence Scale and amount of ‘*snus*’ used at baseline.

Effect modification analyses will be performed for the two primary outcomes and the following potential effect modifiers measured at baseline: gender, average number of cigarettes smoked weekly, amount of ‘*snus*’ used weekly, and severity of dependence as measured by Fagerström’s Nicotine Dependence Scale. Each effect modification will be assessed by adding the appropriate interaction term to the adjusted regression model. Consideration for adjustment for multiplicity of comparisons will be discussed. All tests will be performed 2-sided with a 5% level of significance.

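### Complete-case analysis of 7-day abstinence drops SMS-stage responders, although their 4-week answer settles or strongly informs their 7-day status

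*Protocol article*

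**What the plan says.** Under Outcome evaluation, follow-up runs in stages: an emailed questionnaire, two weekly reminders, three further Emails, text messages, and finally phone calls. On the text-message stage the protocol says: "If still not responding, the non-responders will receive a SMS every second day for 6 days". That message comes "with only 2 questions to answer, to capture the 2 primary outcome measures". The phone stage follows ("Lastly, those still not responding will be phoned with a maximum of 10 calls per participant"), but the article does not say which outcomes the caller asks about.

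The second primary outcome is "Self-reported 4-week point prevalence of smoking abstinence (not having smoked a single cigarette"). The first secondary outcome is 7-day abstinence, "defined as not smoking any cigarettes in the past 7 days". The other three are quit attempts, use of other cessation services, and weekly cigarettes among those still smoking.

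The Data analysis section states that "all analyses will include all participants with follow-up data in their groups as randomised". The Primary analyses section, which also covers the secondary outcomes, states: "The primary analyses will assume that missing outcome data are missing at random and, therefore, will be performed on complete cases only". All regressions adjust for baseline variables only. The Sensitivity analyses section plans a range of informatively missing odds ratios (IMOR, the odds of abstinence in those with missing data relative to those observed), equal in both arms, from 0.5 to 1 and also 0. It adds a repeated attempts model built on the link between quitting and the number of contacts needed.

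**The concern.** The secondary outcomes are missing by design for everyone who first answers by text message. These people do have follow-up data: both primary outcomes. Under the complete-case rule they still leave every secondary analysis, which sits badly with the commitment to include all participants with follow-up data.

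For 7-day abstinence the loss is avoidable in part. By the protocol's own definitions, a 4-week abstainer is a 7-day abstainer. A responder who is not 4-week abstinent has an undetermined 7-day status, but is much less likely to be abstinent than an average responder. The planned model uses neither fact.

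At stake are the precision of the 7-day result, the reported 7-day proportions, and, under some conditions, the odds ratio. The primary and 7-day results would also rest on different sets of people, although the outcomes are close relatives.

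**Working it through.** **Inputs.** From Sample size: 10% against 5%, 80% power, two-sided 0.05, continuity correction, 474 per group, 30% attrition. From Sensitivity analyses: IMOR 0.5 to 1, and 0. Assumptions, because the protocol gives no figure: 10 to 30% of responders answer by text message; the 10%/5% rates also apply to 7-day abstinence; 70% of 7-day abstainers are also 4-week abstinent.

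**The plan's own figure.** Uncorrected: n0 = [1.96√(2 × 0.075 × 0.925) + 0.842√(0.09 + 0.0475)]² / 0.05² = 434.4. Corrected: n = (n0/4)[1 + √(1 + 4/(n0 × 0.05))]² = 473.6, so 474 as stated. Then 474/0.7 = 677.1, against 677 stated; 2 × 677 = 1,354. Nothing here is disturbed.

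**How many are dropped.** 474 × 0.10 = 47; 474 × 0.30 = 142 per arm. At a 20% share, 474 × 0.20 = 95 per arm. If 10% and 5% of these are 4-week abstinent, about 9 intervention and 5 control participants with known 7-day abstinence are left out.

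**Precision.** Power = Φ{[0.05 − 1/n − 1.96√(0.13875/n)] / √(0.1375/n)}.

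| Text-message share | n per arm | Power |
|---|---|---|
| 0 | 474 | 80.0% |
| 5% | 450 | 77.8% |
| 10% | 427 | 75.4% |
| 20% | 379 | 69.8% |
| 30% | 332 | 63.3% |

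**Bias, arms alike.** The complete-case odds ratio is (0.10/0.90)/(0.05/0.95) = 2.111. For text-message responders, multiply the odds by the IMOR and mix by share.

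- IMOR 1: 2.111 among all responders, so no bias.
- IMOR 0.5, share 10 to 30%: 2.108 to 2.104. The absolute difference falls from 5.0 to between 4.8 and 4.3 points.
- IMOR 0, share 10 to 30%: 2.099 to 2.075. The absolute difference falls to between 4.5 and 3.5 points.

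**Bias, arms different.**

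- Share 20%, IMOR 0.5 in the intervention arm and 1 in the control arm: 1.89. Reversed: 2.35.
- IMOR 0.5 in both arms, share 20% (intervention) against 10% (control): 1.99. Reversed: 2.23.

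**What imputation recovers.** Take share 20%, IMOR 0.5 (intervention) and 1 (control).

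1. Among intervention Email responders, 7% are 4-week abstinent, so the 7-day rate in the rest is 0.03/0.93 = 3.2%, against 10% overall.
2. Intervention text-message responders have a true 7-day rate of 5.26%, of whom 0.7 × 5.26% = 3.68% are 4-week abstinent. Imputing the rest gives 3.68% + 96.32% × 3.226% = 6.79%.
3. Intervention overall: 0.8 × 10% + 0.2 × 6.79% = 9.36%. The true value is 9.05%. Control stays at 5%.
4. Imputed odds ratio: (0.0936/0.9064) × 19 = 1.96, against 1.89 true and 2.11 from complete cases. Share of the bias removed: (2.11 − 1.96)/(2.11 − 1.89), about two thirds.

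A simulation under the same assumptions agrees: 1.91 among all responders, 2.14 from complete cases, 1.98 imputed. Imputation also cut the standard deviation of the log odds ratio from about 0.295 to 0.276.

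**Why not fill in only the known abstainers.** Inclusion would then depend on the outcome. At a 20% share the rates become (0.08 + 0.014)/(0.80 + 0.014) = 11.5% and (0.04 + 0.007)/(0.80 + 0.007) = 5.8%, instead of 10% and 5%. The odds ratio stays at 2.111 if the 70% holds in both arms, but becomes 2.205 if it is 70% against 50%.

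**The case against.** A reader might infer that the text-message stage breaks the missing-at-random assumption. The documents do not support that. Reaching this stage depends on earlier non-response; the assumption fails only if these responders differ in outcome given arm and baseline covariates. The protocol treats this as a question to explore, and an open question is not evidence of a violation. With arms alike, the odds ratio is almost unbiased.

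A reader might also infer that all the lost secondary data can be recovered. They cannot. Only 7-day abstinence follows from a primary answer, and only for 4-week abstainers. Prolonged abstinence allows up to five cigarettes, so it does not settle 7-day status. Quit attempts and service use cannot be deduced at all.

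Three further objections carry weight. The article does not expressly rule out deriving the 7-day value; its exclusion is inferred from the rule that the analyses "will be performed on complete cases only". A short late contact is a reasonable trade to protect the primary outcomes. And no figure for the text-message share is given, nor any statement that it differs by arm.

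The planned sensitivity analyses answer only part of this. They are framed around quitting and the main analysis, and do not mention secondary items missing because of the short message. The IMOR is held equal in both arms, the setting in which the odds ratio moves least. If missing were counted as smoking for the 7-day outcome, people who reported 4 weeks without a cigarette would be coded as smokers.

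**Conclusion.** The point holds in a limited form. The protocol fixes a complete-case, baseline-adjusted analysis for an outcome that is uncollected by design in text-message responders, while it holds an answer from those same people that settles or strongly informs that outcome. This conflicts with its statement on who is included in all analyses.

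The certain cost is precision: at an assumed 10 to 30% share, power for a 10% against 5% contrast falls from 80% to between 75% and 63%. The 7-day proportions are distorted if late responders differ. The odds ratio is materially biased only if that difference, or the share, varies by arm; the range shown is 1.89 to 2.35 against 2.11. All these sizes rest on assumed shares and rates. If phone respondents also answer only the primary questions, the excluded group is larger.

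The primary outcomes and the sample size are unaffected.

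**What to change.** - **7-day abstinence:** analyse everyone with a primary outcome, using multiple imputation by arm. Put both primary outcomes and the planned baseline covariates in the imputation model, and set 7-day abstinence to yes where 4-week abstinence is yes. Do not fill in only those cases. Report complete cases as a sensitivity analysis.
- **Number of contacts:** leave it out of the imputation model unless phone respondents supply secondary outcomes. Otherwise nobody beyond the Email stage has observed secondary data, and the model would extrapolate.
- **Quit attempts and service use:** the same imputation is at most a sensitivity analysis.
- **Wording:** state which outcomes the phone call collects, and reconcile the inclusion statement in Data analysis with the complete-case rule in Primary analyses.

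The cost is a small amount of extra analysis and a few sentences of plan text; no new data are needed. One assumption remains: text-message responders who are not 4-week abstinent resemble Email responders in the same arm with the same primary answers and covariates. In the worked example, this is why about a third of the bias stays.

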### Participants, setting and recruitment

All 25 student health care centres responsible for preventive services for students in Sweden will participate in recruiting interested smokers during a 4-week period in October 2014, through advertisement at strategic places in each college and university. This includes leaflets, posters and information on the local website and in some cases the official Facebook account. Participants register their interest in taking part in the study by sending a SMS to a dedicated telephone number. Interested students will receive mail with more information about the study and how to participate. Also, 19 student health care centres will send an invitation by Email to all students at the end of October 2014 with 2 reminders with 1 week apart, allowing the participants to respond up to 7 days after the last reminder. This means that recruitment of participants will be finalised at the end of the second week of November 2014. A flowchart of the study recruitment procedure is given in Figure 1. Eligible participants are students who are daily or weekly smokers and willing to set a quit date for smoking cessation within the next 4-week period. Exclusion criteria are non-smokers/occasional smokers not smoking every week, and smokers not willing to set a quit date within 4 weeks.

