### Randomisation and other study procedures

Smokers who respond to the invitation Email and want more information about the study will be referred to a page with more information about the study emphasising that only students who are daily or weekly smokers willing to set a stop date within a month are eligible for the study. Most previous SMS-based smoking cessation studies have used the inclusion criteria - willing to set a stop date with 2 to 4 weeks - facilitating recruitment of a more engaged population both in the intervention and control group and thereby avoiding a larger drop-out of randomised participants before the specified quit date [15,18,23].

By emphasising that participants should be willing to set a stop date this would prevent randomised participants dropping out of the study before completing the intervention. After having read the information about the study all participants gave informed consent to participate by clicking on a link. After informed consent was obtained the participants were guided to a baseline assessment page. The hyperlink contained within the body of the Email is no longer valid after completion of the questionnaire when the responses are stored in the study database. This prevents multiple responses, while allowing the questionnaire to be completed in more than one session if required. After completion of the baseline assessment the students will be asked to provide their telephone number. Then they will immediately receive a SMS that will have to be responded to by writing, ‘start’, in order to confirm that they had stated the right telephone number.

Participants will immediately be randomised to an intervention or waiting list (control) group. Each participant is allocated a number 1 or 2 with equal probabilities using Java’s built in random number generator (java.util.Random). Randomisation is thus fully computerised, does not employ any strata or blocks, and is not possible to subvert, as this and all subsequent study processes are fully automated.

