## Trial status

At the time of submission the recruitment of participants had started but is not yet complete. Recruitment will be completed on the 14 November 2014.

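### Use of other cessation services is counted from the first invitation, not from randomisation, which modestly dilutes the comparison for hypothesis 5

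*Protocol article*

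**What the plan says.** The secondary outcomes listed under Outcome evaluation include two counts with different starting points. Quit attempts are defined as "Mean number of quit attempts since taking part in the study". Uses of other cessation services are defined by a list of service types that ends "calling the help-line or any other help) since first invitation to the study". Under Primary analyses both counts go into the same kind of model, negative binomial regression reported as a ratio of means. Both are adjusted for gender, years of smoking, weekly cigarettes, Fagerström score and snus use. Earlier use of cessation services is asked about at baseline but is not in that adjustment set.

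On timing, the section on participants and recruitment describes "recruiting interested smokers during a 4-week period in October 2014, through advertisement at strategic places in each college and university". It then says that 19 of the 25 centres "will send an invitation by Email to all students at the end of October 2014 with 2 reminders with 1 week apart". Replies are accepted for a further week once the second reminder has gone out. Trial status adds: "Recruitment will be completed on the 14 November 2014". The section on randomisation places an information page, consent, the baseline questionnaire and confirmation of the telephone number between the invitation and allocation.

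**The concern.** Hypothesis 5 is that the intervention group makes greater use of other cessation services. A service used between the invitation and randomisation cannot be a result of allocation. Counting it adds the same expected amount to both arms, and a ratio of means moves towards 1 when the same amount is added to numerator and denominator. The planned covariates do not remove this.

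Three features of the definition make it look unintended. The neighbouring count has a different origin, and no reason is given. Use between invitation and baseline can be recorded twice, once as baseline history and once as outcome. And the article does not say what counts as the first invitation for a student who came in through a poster, a leaflet or a website, so the length of the pre-randomisation window depends on the recruitment route and on how the participant reads the question.

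**Working it through.** The article gives no figure for service use or for the delay from invitation to randomisation, so there is no stated result to reproduce on this outcome. The one planning figure used below, 474 per group, does reproduce: 10% versus 5%, two-sided 0.05, 80% power and continuity correction give 474.

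**Step 1: what the invitation is.** The section on randomisation speaks of "Smokers who respond to the invitation Email and want more information about the study". The section on earlier feasibility work says "recruitment should not only to be by invitation by mail, but also through posters, leaflets and information on the colleges’ and universities’ homepages", which sets the mailed invitation apart from the advertising. In the article's own usage, then, the invitation is the Email.

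**Step 2: longest possible lag.**
- Email, by the stated schedule: 7 + 7 + 7 = 21 days = 3.0 weeks.
- Email, by calendar to 14 November: 14 days = 2.0 weeks if sent on 31 October; 21 days = 3.0 weeks if sent on 24 October (both sending dates assumed).
- Advertising, if it counted as the invitation: 1 October (assumed start) to 14 November = 44 days = 6.3 weeks.

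**Step 3: dilution.** Let F be the follow-up time: 4 × 365.25 / 12 / 7 = 17.39 weeks. Let w be the mean lag in weeks, RR the true ratio after randomisation, and r the rate of use before randomisation relative to the control rate afterwards. RR and r are assumptions. Then

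observed ratio = (r·w + RR·F) / (r·w + F).

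With RR = 1.50, RR·F = 26.09. For r = 1:

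| Mean lag w | Calculation | Observed ratio | Share of control count before randomisation |
|---|---|---|---|
| 0 | 26.09 / 17.39 | 1.50 | 0% |
| 1 week | 27.09 / 18.39 | 1.47 | 5% |
| 2 weeks | 28.09 / 19.39 | 1.45 | 10% |
| 3 weeks | 29.09 / 20.39 | 1.43 | 15% |

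If the earlier rate is half the control rate (r = 0.5), 3 weeks gives (1.5 + 26.09) / (1.5 + 17.39) = 1.46. If the invitation itself prompts people to seek help, r exceeds 1 and the dilution is larger. At RR = 1 the formula returns 1 for any w and r, so the null is preserved.

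**Step 4: power, as an illustration.** Take 474 per arm, control mean m0 and intervention mean m1 over the whole counting window, dispersion k, and Var(log ratio) = (1/m0 + k)/474 + (1/m1 + k)/474. Assume a control mean of 0.5 over follow-up, k = 2, RR = 1.5 and r = 1.
- w = 0: m0 = 0.50, m1 = 0.75; log ratio 0.405, standard error 0.124; power 90%.
- w = 3: m0 = 0.586, m1 = 0.836; log ratio 0.355, standard error 0.121; power 84%.

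The standard error falls slightly, so the loss comes from the smaller ratio and not from added noise. Over control means of 0.3, 0.5 and 1.0 and dispersions of 1 and 2, with RR = 1.5, the loss at a 3-week mean lag runs from about 1 to 8 percentage points.

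**The case against.** The strongest reply is that the lag is short for most people. The steps from information page to allocation are automated, and a student who answers the first Email at once may have a lag close to zero. The formula needs the mean lag, whereas 3 weeks applies only to the last possible Email responder. No response distribution is given, so the mean is unknown, but it must lie below the maximum. This stands, and the 3-week row should be read as a ceiling for the Email route.

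A reader might infer a window of up to about six weeks, since advertising ran through October; at 6.3 weeks the formula gives 1.37 for a true 1.50. The documents do not support that as the general case. It requires the advertising to count as the invitation, which is not how the article mostly uses the word, and it then describes only someone who saw the first advertisement and was randomised last. Students who registered by SMS after seeing an advertisement were also to be sent individual mail with study information, so they too have a datable contact. What remains is that the term is left undefined for them, and that 25 − 19 = 6 centres are not listed as sending an Email invitation.

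A reader might also infer bias between arms or false positives. Randomisation balances earlier use, and the varying window lengths are independent of allocation, so neither follows.

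Finally, the follow-up questionnaire is not shown and may carry a clearer anchor. That is fair: only the outcome definition can be criticised.

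**Conclusion.** The point holds as a modest flaw in one stated definition. The window for service use opens before randomisation, by up to about 2 to 3 weeks on the Email reading, and the estimated ratio for hypothesis 5 is pulled towards 1 as a result. For a true ratio of 1.50 the estimate would be about 1.47 to 1.43 for mean lags of 1 to 3 weeks, assuming a constant rate of use and 17.4 weeks of follow-up. It is nearer 1.50 if the mean lag is under a week or if use before joining is rarer. The effect is confined to one of four secondary outcomes. The primary outcomes, the sample size and the type I error rate are untouched.

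**What to change.** Define the outcome as the number of uses of other cessation services since randomisation, and state the same anchor for quit attempts so that the two counts cover the same period. Word the follow-up item to match, for example 'since you joined the study on [date]', with the participant's own randomisation date filled in. This removes the dilution (w = 0) and the need to define the first invitation for each recruitment route.

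The cost is one line of outcome definition and, if the unseen questionnaire item uses the invitation as its anchor, one line of item wording. Trial status says that recruitment was still open at submission. Follow-up questionnaires go out at 4 months, so on the article's own timetable the change could be made before any were sent. Nothing needed for hypothesis 5 is lost.
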